## Abstract

**Background:**

Patients with RA (Rheumatoid Arthritis) are more sedentary than the general population. Reduction of Sedentary Behaviour (SB) has been suggested as a mean for improvement of health in patients with chronic diseases and mobility problems. Short-term intervention studies have demonstrated that SB can be reduced by behavioural interventions in healthy populations. However, it remains unexplored whether it is valid for patients with RA also.

Therefore, the aim of this trial is to investigate the efficacy of an individually tailored, theory-based motivational counseling intervention on reducing daily sitting time in sedentary patients with RA. Additionally, to explore whether a reduction in daily sitting time is associated with reduced pain and fatigue, self-reported physical function, self-efficacy, improved health-related quality of life (HR-QoL) and cardiovascular biomarker levels, and finally to assess the cost-effectiveness of the intervention.

**Methods/Design:**

For this parallel group randomized trial, 150 patients with RA and at least 5 hours of sitting time per day, will be recruited from a rheumatology outpatient clinic, and block-randomized to the intervention group or the control group receiving usual care. The intervention includes: 1) individual motivational counseling (in total 3 sessions) on reduction of daily sitting time in combination with 2) individual Short Text Message Service (SMS) reminders over a 16-week intervention period. Primary outcome is change in daily sitting time (minutes) from baseline to 16 weeks measured objectively using an ActivPAL® Activity Monitor. Secondary outcomes include fatigue, pain, physical function, HR-QoL, self-efficacy, costs and cost-effectiveness. Furthermore, anthropometric measures will be included as well as measurement of blood pressure and serum lipids. All outcomes are assessed at baseline and repeated after 16 weeks. Follow-up assessments are made at 6 and 18 months post-intervention.

**Discussion:**

The intervention is simple, non-invasive and may be implemented at low costs. If the study confirms the positive results expected, the intervention might be implemented in clinical practice and potentially transferred to other clinical populations.

**Trial registration:**

ClinicalTrial.gov registration number: NCT01969604. Date of registration: 17 October 2013.

## Background

### Background and rationale

Physical inactivity is an established risk factor for chronic disease and premature death [1,2]. In addition to physical inactivity, an increasing number of population-based observational studies [3-5] have shown that sedentary behavior is a distinct and independent risk factor for cardiovascular morbidity and mortality. Patients with rheumatoid arthritis (RA) have an increased risk of cardiovascular disease and premature death [6,7]. The increased risk is partly caused by the chronic inflammatory rheumatic disease itself and partly by traditional risk factors; for example, hyperlipidemia and hypertension, but may also be attributed to physical inactivity [8,9]. In Denmark, 67% of patients with RA do not meet the public health recommendations for daily moderate and vigorous physical activity (MVPA), and similar proportions of physically inactive RA patients are found in Germany (68%) and the United Kingdom (67%) [9].

The everyday life of patients with RA is periodically influenced by increased disease activity (flares) with symptoms such as swelling and stiffness of the joints accompanied by intense pain, which can lead to severe limitations in physical functioning and potential progressive joint destruction [10,11]. Intervention studies in patients with RA have documented a positive effect of exercise on pain and physical functioning [12,13]. However, studies have also demonstrated that exercise and increased activity levels are difficult to maintain over time [12,13] and have identified pain as a main barrier against adaptation and maintenance of a physically active lifestyle in patients with RA [14]. Sedentary behavior has been defined as any waking behavior characterized by an energy expenditure ≤ 1.5 METs (Metabolic Equivalent of Task) while in a sitting or reclining position [15]. Such behavior has become increasingly prevalent in modern society, and recent population studies [16,17] using self-reported questionnaires estimate a mean daily sitting time of 8 to 9 hours, corresponding to 50 to 60% of waking hours. Likewise, a US population-based study among 4,757 adults measured objectively daily sitting time to be on mean 8.44 hours [18]. A few studies have measured sitting time objectively in patients with chronic disease, and these studies generally find that patients with various types of physical disability have higher proportions of sitting time during waking hours; for example, stroke (86 to 88% of waking hours) [19], multiple sclerosis (75 to 85% of waking hours) [20] and Parkinson’s disease (76% of waking hours) [21]. In RA patients, Pioreschi *et al*. found that 71% of waking hours were spent sedentary compared to 62% of waking hours in healthy controls [22]. Objective measures of physical activity and sedentary behavior have been applied in a few other studies in RA patients [23-25]. A review from 2011 suggests that aiming to increase physical activity levels among patients with physical disability should not solely focus on increasing MVPA (moderate and vigorous physical activity) but should also target reduction of sedentary behavior and increase in light intensity activity as this approach may prove feasible for improving health and well-being [26].

A few short-term intervention studies applying objective measures of sitting time in older people [27], and in overweight or obese adults [28,29] have demonstrated that sedentary behavior can be reduced through behavioral intervention [27,28] and that physical activity energy expenditure may be increased by reduction of TV-viewing time [29]. Accordingly, we hypothesize that sedentary behavior can be reduced through lifestyle change in patients with RA.

### Objectives

The primary objective of this trial is to investigate the efficacy of an individually tailored, theory-based motivational counseling intervention on reducing daily sitting time in sedentary patients with RA. The secondary objectives are to explore whether a reduction in daily sitting time is related to reduction in pain and fatigue, improved health-related quality of life (HR-QoL), self-reported physical function, self-efficacy and improved cardiovascular biomarker levels, and to assess the cost-effectiveness of the intervention.

## Methods

### Trial design

The current study is part of the ‘Joint Resources’ research program devoted to health promotion studies in patients with RA [30,31] and initiated in 2009 at Glostrup Hospital. The study is designed as a randomized, controlled, observer-blinded trial with two parallel groups and a primary endpoint of changes in objectively measured daily sitting time. Patient-reported outcomes and other measured variables will be collected before randomization, soon after the intervention (after 16 weeks), and 6 and 18 months post-intervention. Randomization will be performed with a 1:1 allocation (blocks of 10 patients) [32].

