### Recruitment, screening and enrollment

The patients will be recruited from the Danish National Board of Health biological therapies (DANBIO) database, a nationwide registry that has included > 30,000 patients with inflammatory arthritis in a longitudinal observational cohort [37]. The patients will be screened for diagnosis code and the latest HAQ score in DANBIO (Figure 1). In accordance with the guidelines of the Danish Research Ethics Committee, potentially eligible patients will receive a letter with an invitation to participate, an information leaflet and a folder with basic information about trials and personal rights. A few days later the Project Leader (TT) will contact them by telephone and inquire whether they are interested in participating in the study. If interested, patients answer two ‘screening questions’ on 1) self-reported daily sitting time during leisure time and work, and 2) self-reported participation in vigorous physical activity (both questions are from the Physical Activity Scale (PAS 2.1)) [34] to assess eligibility. If eligible, the patients will be invited to an information session with the Project Leader. It will be possible for the patients to sign the consent form immediately following the session or during the following 2 days. Informed consent will be obtained from each patient prior to the trial.

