### Randomization and blinding

Immediately following the baseline measurements, randomization to either (A) the intervention group (N = 75) or (B) the control group (N = 75) will be performed via computer-generated ‘random numbers’ for each of the 2 groups (blocks of 10 patients). Patients will be informed by TT about their group allocation 1 week after baseline measurements. Patients will not be blinded to the intervention; however, all measurements will be conducted by two occupational therapists who will be blinded to group allocation.

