Baseline demographic characteristics of patients are collected (electronically) via a self-report questionnaire (using tablets). Two occupational therapists will attach the ActivPAL® monitor [41] and instruct patients in how to wear the monitor 24 hours per day for 7 days. All ActivPAL® will be coded to start from midnight following the first day of application. One week (7 days) after baseline measurements the patient will return to the hospital for removal of the ActivPAL®. At the same time the patient will be informed by the Project Leader (TT) about the group allocation. One week after each of the follow-up measurements the patients will return the ActivPAL® in a closed envelope. During each 7 day-period with ActivPal® the patients fill a diary about their resting time and sleeping time in order to isolate their sitting time from sleeping time. At each medical visit to the outpatient clinic, the treating rheumatologist registers information in DANBIO including data regarding disease characteristics (for example, patient-reported outcomes, disease activity, functional status, disease course) and medical treatment [37]. Patients will not be blinded to the intervention; however, all assessors will be blinded for the two participating groups.

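### A fixed, published block of 10, with the recruiter also disclosing allocations, leaves a modest and avoidable route to selection at enrolment

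*Protocol article*

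**What the plan says.** **Sequence.** The Trial design section says "Randomization will be performed with a 1:1 allocation (blocks of 10 patients". Randomization and blinding repeats one block size, with computer-generated numbers "for each of the 2 groups (blocks of 10 patients", and names the arms as "A) the intervention group (N = 75) or (B) the control group (N = 75". That makes 15 blocks over 150 patients. Study setting gives one outpatient clinic.

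**Who recruits.** In Recruitment, screening and enrollment, the Project Leader telephones candidates, and the two self-reported screening questions belong to that contact. Then: "If eligible, the patients will be invited to an information session with the Project Leader". Consent may be signed straight after that session or within 2 days.

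**Who discloses.** Under Data collection, at the visit where the monitor is removed: "At the same time the patient will be informed by the Project Leader". Randomization and blinding agrees that the same role tells patients "about their group allocation 1 week after baseline measurements".

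**Blinding and timing.** "Patients will not be blinded to the intervention"; the two measuring occupational therapists are blinded. Randomization is placed after baseline: "Immediately following the baseline measurements, randomization to either" one of the two groups. The Intervention section, however, puts the first counseling session directly after randomization.

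**The concern.** The stated blinding covers the people who measure, not the person who recruits. The role that speaks to candidates before consent also learns each allocation when passing it on. With one known block length and one sequence for the whole trial, disclosed allocations show how many places each arm has left in the current block. Hiding the list would not prevent this, because the information comes from the disclosures.

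The intervention is motivational counseling with goals that patients set themselves, so motivation is a plausible determinant of the primary outcome. A recruiter who leans toward one arm for the next place could, even without intending to, encourage, delay or discourage a candidate. Intention-to-treat analysis, a device-based outcome and blinded assessors do not correct selection at entry. The planned ANCOVA adjusts for the baseline value of the outcome, not for motivation.

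**Working it through.** The article gives no figure on predictability, so there is none to reproduce. Its sample-size figures, which supply the 50-minute target used in step 5, do reproduce with the pooled t-test (SD 102 minutes): power is 80.4% at 67 per arm and 84.7% at 75.

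**1. Inputs.** Block of 10 with 5 per arm, so C(10,5) = 252 equally likely sequences; 15 blocks; recruitment from April 2013 to December 2014 (Trial status).

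**2. Worst case: all earlier allocations known, block boundaries known.**
- An assignment is certain once one arm has used its 5 places. After k allocations the probability of this is 2·C(k,5)/252. Summing over k = 5 to 9 gives 2(1 + 6 + 21 + 56 + 126)/252 = 420/252 = 1.67 per block. That is 16.7%, or 25 of 150.
- Always guessing the arm with more places left gives 5 + 2^9/252 − 0.5 = 6.53 correct per block. That is 65.3%, or about 98 of 150 against 75 by chance.

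**3. With recent allocations undisclosed.** Twenty to 21 months is about 87 to 91 weeks, and 150 patients over that time is 1.6 to 1.7 per week. This average rate is an assumption. The one-week delay then hides about 1 to 2 allocations. The interval from telephone call to baseline adds patients whose assignments are not yet made, so 3 is also plausible. Each undisclosed allocation removes the last term from the first sum. Enumeration of all 252 sequences gives the correct-guess rates.

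| Undisclosed | Certain per block | Certain | Of 150 | Best guess correct |
|---|---|---|---|---|
| 0 | 420/252 | 16.7% | 25 | 65.3% |
| 1 | 168/252 | 6.7% | 10 | 60.3% |
| 2 | 56/252 | 2.2% | 3.3 | 58.1% |
| 3 | 14/252 | 0.6% | 0.8 | 55.9% |

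**4. Effect of varying the block size.** Simulated for a guesser who knows the set of sizes but not their order, with nothing undisclosed:
- 8/10/12: 1.4% certain, 65.1% correct
- 6/8/10: 1.6% certain, 66.3% correct
- 4/6/8: 2.3% certain, 68.0% correct

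Varying sizes removes nearly all certainty but hardly changes the best-guess rate, and smaller blocks raise it.

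**5. Illustration in minutes (assumption, no source in the document).** Suppose every enrolment were steered so that the expected outcome shifts by η in the guessed direction. With a proportion p of guesses correct, the bias in the group difference is 2η(2p − 1). For η of 10 to 25 minutes, that is about 6 to 15 minutes at p = 0.653 and 4 to 10 minutes at p = 0.60, against the 50-minute target.

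**The case against.** A reader might infer that the Project Leader knows every earlier assignment when approaching the next candidate, so that 25 of 150 assignments are known in advance. The document does not say this. It says only that this role informs patients a week after baseline. Between the call and randomization lie the information session, up to 2 days to sign and the baseline measurements. Refusals and delays in that interval also blur which place in the block a candidate will take. This objection stands: the worst case is an upper bound, not an expectation.

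A reader might also infer that allocation is unconcealed. The article does not say who generates or holds the list, and a condensed article may leave that to the full protocol, so the silence is no finding. Randomization after consent and baseline is already planned. Nothing suggests that steering occurred or was intended.

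Ten is also a fairly large block. With all earlier allocations known, a fixed block of 4 gives 33.3% certain and 70.8% correct, and a block of 6 gives 25.0% and 68.3%. Candidates come from registry lists and mailed invitations, and non-participants are logged by category, so selective exclusion would leave some trace.

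These points reduce the size of the risk. They do not remove the stated combination: one published block length, and one role that both recruits and learns allocations.

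**Conclusion.** The point holds as a modest, avoidable risk. Later assignments are partly predictable to the recruiter. At most 16.7% are certain and 65.3% guessed correctly. More realistically, about 0.6% to 6.7% are certain (about 1 to 10 of 150) and 56% to 60% are guessed correctly, against 50% by chance. The lower range assumes steady recruitment at about 1.7 patients per week, and that the Project Leader learns each allocation only when disclosing it.

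Which case applies cannot be settled from the article. Randomization directly after baseline, first counseling directly after randomization, and disclosure one week after baseline do not fit together as written, and this timing sets the number of undisclosed allocations. Any bias in minutes depends on an assumed steering effect and should not be read as an estimate.

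**What to change.** 1. Have existing staff who take no part in recruitment tell patients their allocation, so that the Project Leader does not learn assignments while recruiting. This is the main step. The two measuring occupational therapists cannot take it on without losing their blinding.
2. For patients not yet randomized, generate the remaining sequence with randomly varying block sizes, for example 8, 10 and 12, and do not disclose the sizes to recruiting staff. This removes nearly all certain assignments, but alone leaves the best-guess rate near 65%.
3. Reconcile the Intervention section's timing of the first session with the disclosure timing in Randomization and blinding and in Data collection.

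The cost is one reassigned task, a new computer-generated list, and arms that may end a few patients away from 75 and 75. The outcome, the sample size and the analysis model need no change.

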### Study setting

Patients will be recruited from lists of RA patients from the rheumatology outpatient clinic at Copenhagen University Hospital, Glostrup, the Capital Region of Denmark (approximately 2,000 patients per year).

### Eligibility criteria

#### Inclusion criteria

Patients can be included in the study if they have been diagnosed with RA (defined by the American College of Rheumatology (ACR) 1987 criteria [33]), are over the age of 18, have self-reported sitting time of 5 hours or more per day (measured by Physical Activity Scale), (PAS version 2.1) [34] have a physical function score < 2.5 (measured by Health Assessment Questionnaire, HAQ [35]), are able to give informed consent, understand and speak Danish, and have access to a mobile phone.

#### Exclusion criteria

Patients will be excluded from the study if they have severe physical disability (HAQ score > 2.5) that would prevent them from reducing daily sitting time (for example, use of wheelchair); are pregnant; participate in vigorous physical activity in their leisure time for more than 8 hours a week (measured by PAS 2.1). Excluded patients or eligible ones who do not want to participate will be registered in one of the following three categories: 1) not meeting the inclusion criteria, 2) refused to participate, or 3) other reasons [36].

### Recruitment, screening and enrollment

The patients will be recruited from the Danish National Board of Health biological therapies (DANBIO) database, a nationwide registry that has included > 30,000 patients with inflammatory arthritis in a longitudinal observational cohort [37]. The patients will be screened for diagnosis code and the latest HAQ score in DANBIO (Figure 1). In accordance with the guidelines of the Danish Research Ethics Committee, potentially eligible patients will receive a letter with an invitation to participate, an information leaflet and a folder with basic information about trials and personal rights. A few days later the Project Leader (TT) will contact them by telephone and inquire whether they are interested in participating in the study. If interested, patients answer two ‘screening questions’ on 1) self-reported daily sitting time during leisure time and work, and 2) self-reported participation in vigorous physical activity (both questions are from the Physical Activity Scale (PAS 2.1)) [34] to assess eligibility. If eligible, the patients will be invited to an information session with the Project Leader. It will be possible for the patients to sign the consent form immediately following the session or during the following 2 days. Informed consent will be obtained from each patient prior to the trial.

**Figure 1 Fig1:**
[figure not shown]
**Recruitment, screening, enrollment, and randomization.** Figure 1 illustrates the procedure of recruitment, screening, enrollment and randomization of patients in the trial.

### Feasibility study and power calculation

A feasibility study has been conducted with the aim of testing and evaluating selected methods and instruments for this trial, as well as testing all elements of the planned study (November 2012 to May 2013). The feasibility study included 19 patients with RA with an average daily sitting time at baseline of 10.13 ± 1.7 hours (mean ± SD). The SD for calculation of sample size in the current trial was based on ActivPAL® data from the feasibility study measured as total daily sitting time. We expect a reduction in average daily sitting time of 50 minutes in the intervention group. This estimated reduction in sitting time is based on a US pilot study from 2012 on obese office workers who reduced their daily sitting time by 48 minutes as a result of a behavioral intervention [28]. For a 2-sample pooled *t*-test of a normal mean difference with a 2-sided significance level of 0.05, assuming a common standard deviation of 102 minutes, a sample size of 67 RA patients per group is required to obtain a power of at least 80% to detect a group mean difference of 50 minutes. Enrolling a sample size of 75 in the intention-to-treat (ITT) population per group has a reasonable power (84.7%) to detect a mean difference of 50 minutes (SAS Power and Sample Size, v. 3.1; SAS Institute Inc., Cary, NC, USA).

### Randomization and blinding

Immediately following the baseline measurements, randomization to either (A) the intervention group (N = 75) or (B) the control group (N = 75) will be performed via computer-generated ‘random numbers’ for each of the 2 groups (blocks of 10 patients). Patients will be informed by TT about their group allocation 1 week after baseline measurements. Patients will not be blinded to the intervention; however, all measurements will be conducted by two occupational therapists who will be blinded to group allocation.

### Intervention and control group

#### Intervention

The intervention includes: 1) Individual motivational counseling including hand-outs of 4 key messages regarding reduction of daily sitting time [38] in combination with 2) Individual Short Text Message Service (SMS) reminders.Individual motivational counseling

The intervention consists of 3 individual motivational counseling sessions (60 to 90 minutes), conducted by one of the project staff (4 nurses or occupational therapists), who have been trained and calibrated in motivational interviewing (MI) techniques [38] for this specific intervention.

Counselors will simultaneously be trained and supervised by a psychologist to ensure that the intervention will be delivered in a similar way based on the theoretical understanding of MI. The first counseling will take place immediately after randomization to the intervention group, the second will be 2 weeks after, and the third 10 weeks after the first counseling (Figure 1). The motivational counseling sessions will take place in an undisturbed room at the hospital.

